## Abstract

**Background:**

Obese adults struggle to make the changes necessary to achieve even modest weight loss, though a decrease in weight by as little as 10% can have significant health benefits. Failure to meet weight loss goals may in part be associated with barriers to obesity treatment. Wide-spread dissemination of evidence-based obesity treatment faces multiple challenges including cost, access, and implementing the programmatic characteristics on a large scale.

**Aims:**

The PDA+: A Personal Digital Assistant for Obesity Treatment randomized controlled trial (RCT) was designed to test whether a PDA-based behavioral intervention enhances the effectiveness of the existing group weight loss treatment program at VA Medical Centers Managing Overweight/Obese Veterans Everywhere (*MOVE!*). We also aim to introduce technology as a way to overcome systemic barriers of traditional obesity treatment.

**Methods/Design:**

Veterans enrolled in the *MOVE! *group at the Hines Hospital VAMC with BMI ≥ 25 and ≤ 40 and weigh < 400 pounds, experience chronic pain (≥ 4 on the NRS-I scale for ≥ 6 months prior to enrollment) and are able to participate in a moderate intensity exercise program will be recruited and screened for eligibility. Participants will be randomized to receive either: a) *MOVE! *treatment alone (Standard Care) or b) Standard Care plus PDA (PDA+). Those randomized to PDA+ will record dietary intake, physical activity, and weight on the PDA. In addition, they will also record mood and pain intensity, and receive biweekly telephone support for the first 6-months of the 12-month study. All participants will attend in-person lab sessions every three months to complete questionnaires and for the collection of anthropomorphic data. Weight loss and decrease in pain level intensity are the primary outcomes.

**Discussion:**

The PDA+ trial represents an important step in understanding ways to improve the use of technology in obesity treatment. The trial will address barriers to obesity care by implementing effective behavioral components of a weight loss intervention and delivering high intensity, low cost obesity treatment. This RCT also tests an intervention approach supported by handheld technology in a population traditionally considered to have lower levels of technology literacy.

**Trial Registration:**

ClinicalTrials.gov: NCT00371462

## Background

The obesity epidemic is recognized as an increasingly significant U.S. health problem [1]. The percentage of overweight (BMI ≥ 25-29.9 kg/m^2^) and obese (BMI ≥ 30) adults has increased in the U.S. from 46% in 1960 to 74% in 2007-08 [2]. Obesity markedly increases the risk of cardiovascular disease (CVD), cancer, Type 2 diabetes, osteoarthritis, gall bladder disease, sleep apnea, respiratory disease, pain related conditions, and premature mortality [1,2]. In addition to adverse medical consequences, obesity takes a toll on quality of life. Among veterans specifically, BMI in the obese range is significantly associated with presence of self-reported pain [3]. Weight loss efforts are confounded by the comorbid effects of obesity, pain, and the aforementioned health conditions.

Guidelines recommending lifestyle modifications for all obese patients, including diet modification and increased physical activity have been in place for more than 40 years. Yet, fewer than 25% of U.S. adults maintain diet or physical activity in accord with these recommendations [4-6]. A decrease in weight by as little as 10% can have significant health benefits on obesity-related morbidity and mortality [7]. Despite this, few adults can make the changes necessary to achieve even this amount of weight loss. It remains unclear to healthcare professionals what treatment works best to generate achievable weight loss that is cost-effective and easily disseminated.

### Obesity Treatment

There is growing evidence that behavioral treatment and lifestyle interventions are effective in moderate weight loss [8]. National Institutes of Health (NIH) guidelines advise that weight loss and weight maintenance therapy should be based on a comprehensive weight management program, including changes to diet, physical activity, and behavior goal setting [9]. Supporting these guidelines, studies of lifestyle interventions indicate that the most successful determinants are those that include an educational component addressing diet and physical activity, as well as behavior therapy, incentives, and health professional follow-up [10]. It is also recommended that individualized goals be set to reduce body weight at an optimal rate of 0.5 to 1 kg per week for the first 6 months to achieve an overall 10% weight loss [9]. Behavioral counseling has assisted overweight and obese patients to achieve clinically significant (3-5 kg) weight loss that is sustainable for up to 2 years [1,9-11]. However, the treatments that have been proven to work present a number of barriers including cost, access, and large-scale implementation.

### Barriers to Obesity Treatment

The current healthcare system cannot manage the large numbers of patients who need weight loss treatment. Evidence suggests that meaningful obesity treatment must provide individuals with frequent and immediate feedback about diet, exercise, and ways to implement new behaviors in order to achieve weight loss [12]. The costs for these types of treatment are far beyond what individuals and the healthcare system can sustain [12]. U.S. obesity-attributable medical expenditures are estimated at $75 billion annually, with $17 billion financed by Medicare and $21 billion financed by Medicaid [13]. If the trend toward obesity continues, these expenditures will reach up to 16-18% of total U.S. healthcare costs by 2030, equaling $861-957 billion dollars [14]. The challenge for interventions dealing with obesity is to identify how these treatments can be integrated into everyday care in cost effective ways that are not burdensome to patients.

Pain is also considered a barrier in healthy lifestyle interventions, especially in the older population when integrating an exercise component. In the general population and among Veterans, elevated BMI is correlated with reported pain [15,16]. Obesity co-occurs with a number of chronic pain conditions including degenerative arthritis, low back pain, and musculoskeletal pain [17,18]. In combination, pain and obesity have an additive negative effect on health-related quality of life, a finding demonstrated in both patients seeking treatment for obesity[16] and patients seeking treatment for chronic pain [19]. The impact on health care expenditures is substantial because both obesity [20-22] and pain [23,24] are associated with increased care utilization. Healthy lifestyle change is therefore a shared focus of empirically validated treatments for both obesity and chronic pain. The proposed intervention was developed to address the aforementioned barriers to obesity care by delivering effective behavioral components while delivering high intensity, low cost obesity treatment.

### MOVE! Obesity Treatment

Large scale institutions such as Medicare, the National Institutes of Health (NIH), the National Centers for Prevention (NCP), and the Veterans Affairs Medical Centers (VAMC) have all recognized the impact of the obesity epidemic and have developed community-based treatment interventions. One such development is the nationally based Managing Obese Veterans Everywhere *(MOVE!) *program offered at VA medical centers. *MOVE! *is a response to the obesity crisis affecting the veteran population at a significantly higher rate (73% males and 68% females) than the general population (67% males, 62% females) [25]. *MOVE! *is a stepped care program for obesity treatment, using 5-level treatment model. Level 1 implements self-assessment (*MOVE! 23 *questionnaire) and guided self-care. Level 2, targeted for this study, addresses patients who have indicated to their primary care physician or dieticians that they are ready to make behavioral changes in diet and physical activity. Patients receiving Level 2 treatment utilize the Level 1 assessment and self-care strategies, but also participate in group sessions and consultation addressing nutrition, physical activity, and behavior change. *MOVE! *Levels 3 - 5 involve pharmacological, inpatient, and surgical treatments respectively. Levels 1-2 are the most widely implemented delivery formats of *MOVE!*; however they present some practical barriers for those requiring treatment. Veterans identify barriers to participation that includes the time of day the program is offered, and an inability to travel to the hospitals where the program is offered. One potential way to overcome these obstacles is to introduce novel technology that enables cheaper, distance participation and swifter response times as part of obesity treatment.

### Improving Obesity Treatment with Handheld Technology

Self-monitoring has emerged as a critical skill for obesity management [26-28]. Those who report monitoring their weight on a daily or weekly basis have greater success in achieving weight loss goals [7,29-31]. Several studies have shown that PDAs are a reliable tool for dietary self-monitoring and have improved compliance and health indicators (i.e. dietary intake, glucose monitoring, blood pressure) [12,32-34] In spite of these findings, research on the use of handheld technology for self-monitoring behavior, and the impact of integrating a PDA on weight loss into behavioral weight control programs is limited [35]. Handheld technology holds great promise as a mechanism for supporting and disseminating behavioral interventions because they can deliver tailored messages at the point of decision-making in response to the needs of the user at that moment [36,37].

The PDA platform we have developed automatically codes dietary data, and has algorithms that immediately provide real-time feedback about calorie consumption and daily physical activity. Recording dietary intake and activity onto a PDA can motivate timely reporting namely because the user receives immediate feedback relative to their goals. Our technology circumvents the need for pencil and paper reports, which is cumbersome because it requires patients to carry and record onto forms, is prone to significant inaccuracies, and is not subject to timely feedback [26,38]. Another advantage to using handheld technology is that the safety of distance communication may enable patients to feel less self-conscious and freer to report accurately and communicate openly [12,26,33,38]. Installing decision-support tools on the PDA reduces the costs associated with face-to-face meetings with professionals and encourages the regular practice necessary to maintain skill acquisition over time. As a delivery vehicle, the PDA is convenient, removes access barriers, allows tailoring, and disseminates knowledge and expertise in a manner that empowers patients. Our study will implement a PDA that can be integrated into existing care, which may substantially increase the accessibility of an intervention while eliminating the costs associated with intensive weight loss treatment. What is particularly exciting about our study is that we hope to develop a modularized treatment tool that can be independently introduced to programs to increase efficacy and decrease costs.

### Study Aims

The primary aims of the proposed study are to determine whether overweight and obese patients with chronic pain who are randomized to the Standard Care + PDA group (PDA+) show more weight loss over a 6-month period, greater maintenance of weight loss at 12 months, and greater reduction in pain intensity and pain-related disability than those randomized to receive Standard Care only. We hypothesize that the addition of a PDA weight loss decision-support tool for patients plus personalized coaching will improve weight loss, weight loss maintenance, and pain reduction for obese patients with chronic pain, as compared to *MOVE! *standard care.

The secondary aims are to determine whether overweight/obese patients with chronic pain who are randomized to the PDA+ group will show significantly improved quality of life, greater treatment adherence, and reduced care utilization as compared to Standard Care only.

Secondary hypotheses are that the addition of a PDA weight loss decision-support tool for patients plus personalized coaching will improve quality of life and treatment adherence and will reduce health care utilization, as compared to *MOVE! *standard care alone. Ancillary outcomes that will be collected are patient satisfaction, mood, and waist circumference.

## Methods

### Study Design

The research design is a 2 × 5 factorial involving one between subject's factor (treatment condition) with 2 levels (Standard Care vs. Standard Care+ PDA (PDA+) and one within subject's factor (time) with 5 levels (randomization, 3-, 6-, 9-, and 12-month follow-up). Participants will be followed through three trial phases (Figure 1).

**Figure 1 F1:**
[figure not shown]
**PDA+ Trial Phases**.

#### Description of Study Technology

### PDA Technology

Existing diet and activity monitoring technology on the PDA platform is limited. No other available software packages that we know of are theory based, personalized, and can be integrated into pre-existing weight loss programs. Those that are currently in use do not have sufficient empirical support to adapt to a large scale RCT as the one proposed. While the automaticity of feedback is a component of existing technology [7,32], the personalized nature of the daily feedback promises to deliver a more potent intervention.

The PDA tool, a modified version of handheld technology used in the Making Better Choices Study [39], is a patient centered decision-support system that promotes weight loss by helping participants to self-regulate eating and physical activity behaviors. The food database (used for the Nutritionist Pro Nutritional analysis program) contains accurate, up-to-date food and nutrient data for more than 18,000 foods, including brand-name foods, fast foods, and ethnic foods. The PDA program we developed has a user-friendly interface that enables participants to enter food intake and activity information. By converting complex dietary and activity data into two simple energy intake and expenditure thermometers, the PDA system will function as a decision support tool to help people track and make decisions about their momentary behaviors in relation to daily goals. Participants in the PDA+ group will also be oriented to the customizable feedback "thermometers" visually depicting how much of the day's calorie allowance has been used up and what proportion of the day's physical activity goal has been attained thus far.

### Accelerometer Technology

Participants randomized to the PDA+ group will be given an accelerometer (Biotrainer II, IM Systems, Baltimore, MD) to be worn on the hip. This triaxial accelerometer tracks moderate intensity activity by the number of counts displayed, which will provide the study team and participants with an accurate objective measure of physical activity achieved (http://www.imsystems.net/btpro/btpro.htm). The Biotrainer II has been shown to automatically detect changes in physical activity intensity, which is much more accurate than self-report [40]. The Biotrainer II will be individually calibrated for each participant, by walking on a treadmill for five minutes to demonstrate moderate intensity activity to the participant, and to orient the participant to the device display. Participants in the PDA+ group will be instructed to wear the accelerometer at all times except when immersed in water or sleeping, and re-zero the display reading at the end of each day after entry into the PDA.

### Data Collection

Data will be collected at various time points beginning at baseline and continuing through 12-month follow-up on continuous and dichotomous variables using the measures [41-50] in Table 1. Anthropomorphic measures of weight, height and waist circumference will be collected at each in-person session. Participants in the PDA+ group will remotely upload diet, physical activity, pain and mood data to their coach weekly. Data from the accelerometer will be collected at follow-up appointments. Participants will be paid $20 at randomization and at each in-person follow-up session to create an incentive that encourages retention (Total $100).

**Table 1 T1:** Measures

Measures	Baseline	3-month	6-month	9-months	12-months
**Stage of Change**					
**Exercise Stage of Change Short Form**	x	x	x	x	x
**Weight Loss Stage of Change Short Form**	x	x	x	x	x
**Readiness to Change Pain Question**	x	x	x	x	x
**Pain Stage of Change Questionnaire (PSOCQ)**	x		x		x
**Psychological Variables**					
**PRIME-MD**	x				
**Breath Holding Task**	x				
**West Haven-Yale Multidimensional Pain Inventory (WHYMPI)**	x	x	x	x	x
**Distress Tolerance Scale**	x	x	x	x	x
**Numeric Scale of Pain Intensity (NRS-I)**	x				
**Quality of Life (SF-36)**	x	x	x	x	x
**Positive and Negative Affect Schedule (PANAS)**	x	x	x	x	x

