### Recruitment and Screening Procedures

The study procedures are approved by the Institutional Review Board at the Hines VA Medical Center. Participants who pass initial eligibility screening, will then undergo a written informed consent process prior to beginning the study protocol. To be eligible, veterans must be enrolled in the *MOVE! *group at the Hines Hospital VAMC with BMI ≥ 25 and ≤ 40 and weigh < 400 pounds, experience chronic pain ( ≥ 4 on the NRS-I scale for ≥ 6 months prior to enrollment) and are able to participate in a moderate intensity exercise program will be recruited. The enrollment policy is consistent with the 2005 VA/DoD Practice Guideline that recommends obesity treatment for all Veterans with BMI ≥ 25 and consideration of supplemental pharmacotherapy and surgical treatments for severely obese patients with BMI ≥ 40 [51]. Further eligibility criteria is listed in Table 2.

**Table 2 T2:** Eligibility Criteria

Eligibility Criteria
• Willing to participate in a 12-month study
• Independently Mobile (no cane, walker, wheelchair needed)
• Can participate in regular exercise
• No psychiatric hospitalizations within the past year
• No cognitive or sensorimotor impairment
• Cannot participate in a structured diet program outside of study
• Cannot be at high risk for adverse CVD events while exercising
• Considering making changes to lose weight in the next 6 months^1^
• Absence of any substance abuse, mood, or binge eating disorder that would interfere with adherence^2^
• Must experience chronic pain (≥ 4 on the NRS-I scale for ≥ 6 months prior to enrollment)

^1^As measured by the Exercise and Weight Stages of Change Form

^2^As measured by the PRIME-MD

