### Randomization

Prior to randomization and to discourage heightened attrition in the control group, a brief motivational interviewing intervention will be performed to make salient the pros and cons of being randomized to either condition. Participants will be re-assessed about their readiness to make lifestyle changes by administering the Exercise and Weight Stages of Change Short Forms [42] to identify and exclude pre-contemplators.

Participants will be randomly assigned to one of two groups: a) Standard Care or b) Standard Care +PDA (PDA+). Group randomization will be computer-generated via the method of randomly permuted blocks. The use of permuted blocks preserves balance in the randomization over the course of the study, to maintain equal sample sizes in the two experimental conditions. Randomization will be stratified by age (≤ 65 vs. > 65), BMI (< 35 vs. ≥ 35), and gender, to maintain equal numbers of women and men in each treatment condition.

Once randomized, those in the standard care group will no longer record their intake, weight, or activity using the PDA. The group will return all study equipment and attend *MOVE! *groups and follow-up lab sessions as scheduled.

Since the proposed design is additive (i.e., it tests the effects of adding technology and coaching to standard care), it is important to establish that the standard care received by participants is equivalent across conditions (e.g., entails comparable intervention components and level of interventionist expertise). To prevent contamination, *MOVE! *group leaders will be different individuals than those who train and coach participants randomized to the PDA conditions.

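### Pain intensity is a primary outcome, but the NRS-I, the only scale named for it, is scheduled at baseline only, and the article ties the outcome to no repeated instrument

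*Protocol article*

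**What the plan says.** The Abstract (Methods/Design) states: "Weight loss and decrease in pain level intensity are the primary outcomes". Study Aims turns the pain part into a between-arm comparison, with PDA+ expected to show "greater reduction in pain intensity and pain-related disability than those randomized to receive Standard Care only". Intensity and disability are listed there as separate quantities.

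Table 1 (Psychological Variables) lists "Numeric Scale of Pain Intensity (NRS-I") with one mark, at baseline. The same table lists "West Haven-Yale Multidimensional Pain Inventory (WHYMPI") with marks at baseline and at 3, 6, 9 and 12 months. The table does not separate the arms.

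Table 2 uses the NRS-I for entry: "Must experience chronic pain (≥ 4 on the NRS-I scale for ≥ 6 months prior to enrollment").

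On pain recorded through the device, Data Collection says: "Participants in the PDA+ group will remotely upload diet, physical activity, pain and mood data to their coach weekly". For Standard Care, Randomization says that PDA recording stops and "The group will return all study equipment and attend" the usual groups and follow-up sessions. The Abstract adds: "All participants will attend in-person lab sessions every three months to complete questionnaires".

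**The concern.** A between-arm comparison of change in pain intensity needs the same measure, before and after randomization, in both arms. The scale named for pain intensity, on which participants are selected, is not repeated at any scheduled follow-up. The pain ratings that the text describes as repeated after randomization by device come from one arm only.

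If the schedule is followed as printed, the trial cannot report on a primary outcome with its own entry scale. The comparison would then rest on a score from a multidimensional inventory that the article does not designate. Choosing that score later is possible. Recovering NRS-I values from visits already past is not.

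**Working it through.** The plan gives no figure for pain. Its sample size section concerns weight only, so no stated number bears on this point. The check is a reading of the schedule against the aims.

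**1. What the outcome requires.** Study Design has five time levels: randomization and 3, 6, 9 and 12 months. Analysis says that outcomes are modelled longitudinally. A change score needs baseline and at least one follow-up value on the same scale, in each arm.

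**2. Instruments in Table 1 with pain in their name.**

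| Instrument | Timepoints marked | Follow-ups marked | Named for intensity? |
|---|---|---|---|
| NRS-I | 1 of 5 | 0 of 4 | Yes |
| WHYMPI | 5 of 5 | 4 of 4 | No; multidimensional, scores not described |
| Readiness to Change Pain Question | 5 of 5 | 4 of 4 | No; listed under stage of change |
| Pain Stage of Change Questionnaire | 3 of 5 | 2 of 4 | No; listed under stage of change |

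**3. NRS-I.** With 0 of 4 follow-ups, NRS-I change is undefined in both arms: 75 + 75 = 150 participants, none with a change score.

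**4. Pain entries on the PDA.** After randomization PDA+ records pain (Abstract, Data Collection, Weight Loss Phase). Standard Care stops recording and hands back the equipment. Before randomization, the Training and Baseline Period sections list food, weight and activity as the PDA entries, not pain. As described, Standard Care therefore has no PDA pain record, and no between-arm comparison can be built on this source.

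**5. WHYMPI.** It is scheduled at every visit, without restriction by arm, and all participants attend the three-monthly sessions. It is therefore the one available candidate for a repeated pain measure in both arms. The article neither says that one of its scores measures intensity nor names any of its scores as the primary outcome.

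**6. Could the single mark be a printing or extraction loss?** It cannot be excluded, but the NRS-I row has the same form as the other baseline-only rows in its block (PRIME-MD, Breath Holding Task), while neighbouring rows carry all five marks.

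**The case against.** The strongest reply is that the schedule is coherent as it stands. The only use the text gives the NRS-I is as an entry threshold. PRIME-MD, also used for eligibility, is likewise marked at baseline only. On this reading the NRS-I screens and the WHYMPI follows pain over time, and the pairing of intensity with disability in Study Aims suits a multidimensional inventory. No sentence says that the primary pain outcome is change on the NRS-I. Nor does any sentence propose PDA entries for comparing arms; they go to the coach as part of the intervention. Finally, this is a condensed article, and naming a subscale and timepoint is commonly left to the full protocol or analysis plan.

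Much of this stands. A reader might infer that the NRS-I is the only pain-intensity measure in the schedule, so that change in pain intensity cannot be computed in Standard Care. The document does not support that. The WHYMPI is collected in both arms at all five timepoints, and nothing in the article shows that it lacks an intensity score. The NRS-I gap is also not specific to Standard Care; it affects both arms equally. And if the only complaint were that the article does not name a WHYMPI score, it would be missing detail and no finding.

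What the reply does not remove is the schedule itself. Table 1 positively places the one scale named for pain intensity at baseline only, while intensity change is declared primary. A later analysis plan can name a score, but it cannot supply NRS-I values that were not collected.

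**Conclusion.** The point holds in a limited form. Change on the NRS-I, the only instrument named for pain intensity and the scale that defines entry, cannot be computed in either arm: 0 of 4 follow-ups, 0 of 150 participants. PDA pain entries cannot stand in for it. The WHYMPI may supply a pain outcome in both arms, but the article does not tie the primary outcome to it.

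It would go too far to say that a primary outcome has no follow-up data. Whether the trial can measure pain-intensity change from what is already scheduled depends on whether the WHYMPI yields an intensity score, which the article neither confirms nor excludes. For that reason this is a correction worth making, not a critical fault. The conclusion assumes that Table 1 is reproduced correctly and that the full protocol adds no NRS-I assessments.

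**What to change.** Mark the NRS-I at 3, 6, 9 and 12 months in both arms in Table 1, and state that the visit-collected NRS-I is used for the pain-intensity comparison. A single sentence that PDA pain entries are not used to compare arms would remove any doubt on that source.

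The cost is one short scale at four visits that participants already attend to complete questionnaires. Under the plan's attrition of 4% per wave, that is about 150 × (0.96 + 0.96² + 0.96³ + 0.96⁴) = 150 × 3.616 ≈ 542 administrations over the whole trial, with no added visit. It requires an amendment to the schedule, and it cannot be applied to visits already completed.

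If the WHYMPI is the intended endpoint, state the single score that is primary for pain intensity. That costs one sentence and no data collection, but the outcome would then be measured on a different scale from the one used for entry.
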